## Abstract

**Background:**

Patients with primary brain tumours (i.e., neuro-oncology patients) lack access to exercise oncology and wellness resources. The purpose of the Alberta Cancer Exercise – Neuro-Oncology (ACE-Neuro) study is to assess the feasibility of a tailored neuro-oncology exercise program for patients across Alberta, Canada. The primary outcome is to assess the feasibility of ACE-Neuro. The secondary outcome is to examine preliminary effectiveness of ACE-Neuro on patient-reported outcomes and functional fitness.

**Methods:**

Neuro-oncology patients with a malignant or benign primary brain tumour that are pre, on, or completed treatment, are >18 years, and able to consent in English are eligible to participate in the study. Following referral from the clinical team to cancer rehabilitation and the study team, participants are triaged to determine their appropriateness for ACE-Neuro and other cancer rehabilitation services (including physiatry, physiotherapy, occupational therapy, and exercise physiology). In ACE-Neuro, participants complete a tailored 12-week exercise program with pre-post assessments of patient-reported outcomes and functional fitness, and objective physical activity tracked across the 12-week program. ACE-Neuro includes individual and group-based exercise sessions, as well as health coaching.

**Conclusion:**

We are supporting ACE-Neuro implementation into clinical cancer care, with assessment of needs enabling a tailored exercise prescription.

## Background

1

While there is evidence supporting the role of exercise and physical activity for all individuals living with cancer [1], certain tumour groups, including patients with primary brain tumours (i.e., neuro-oncology patients), are underrepresented in this literature [2]. Primary brain tumours are defined as tumours that start in the brain cells. They rarely spread outside of the central nervous system [3]. Patients with primary brain tumours are often presented with poor survival prognoses and undergo intensive treatments that result in cognitive and physical impairments, impacting activities of daily living (e.g., speech, balance, coordination), as well as quality of life [2,[4], [5], [6]]. In Canada, Glioblastoma is the most commonly diagnosed brain cancer in adults [7]. As a cancer population with a median survival of 12–14 months, and 5-year survival rate of 1% for adults over 55 [8], supporting patients to engage in exercise and physical activity may aid in supporting wellness and enhancing quality of life. Other primary brain tumours, even if they grow slowly (i.e., low-grade meningiomas), can significantly affect the quality of life of patients, including the younger adult population. To improve effectiveness, a multidisciplinary collaboration across the medical, rehabilitation, and exercise specialist teams to enhance access to tailored exercise resources is essential [2,9,10].

Exercise work to date in neuro-oncology has been limited, with the few studies supporting exercise feasibility and potential impacts, including decreasing symptom burden and improving physical function, cardiorespiratory fitness, cognition, quality of life, and emotional well-being [[11], [12], [13]]. Given the early state of this literature, work must continue to assess the role of exercise for individuals with brain tumours, and in particular assess the feasibility of implementation into clinical care and how to best tailor exercise based on the unique needs and significant treatment-related side effects that remain a major burden and negatively impact quality of life in this patient population [[14], [15], [16], [17]].

Within Alberta, Canada, we have implemented the Alberta Cancer Exercise (ACE) program [18] over the past five years, and effectiveness is currently being assessed in a dataset of over 2300 participants. However, ACE primarily includes participants from breast, prostate, and colorectal tumour groups. Thus, there remains a critical need for clinical workflows to support building exercise referral into the cancer care system specifically for underserved populations, such as neuro-oncology. Building from ACE, and with a focus on co-creation of tailored programming with patients, clinicians, and researchers, our work aims to [1]: provide a tailored exercise program for neuro-oncology patients, considering addressing needs earlier in the care pathway, from diagnosis through treatment and into longer term survivorship [2]; provide models of delivery of exercise oncology programs to enhance access (i.e., remote delivery, home support, individual vs group); and [3] build this improved access systematically within the neuro-oncology clinics in Calgary and Edmonton, to ensure that all patients diagnosed with brain tumours can access supportive care resources during their cancer care journey. Given the stage of research for exercise oncology in Alberta, an effectiveness-implementation trial [19] in neuro-oncology supports development of a safe and effective program, with changes implemented based on quality improvement feedback from patient and clinical teams as needed throughout the study.

The primary outcome of this work is thus to assess the feasibility of a tailored neuro-oncology exercise program for patients (i.e., ACE-Neuro-Oncology; ACE-Neuro), being treated at the two tertiary cancer centres in Alberta – the Tom Baker Cancer Centre (TBCC) in Calgary, and the Cross Cancer Institute (CCI) in Edmonton. Feasibility includes rates of referral and enrolment, program adherence, measurement completion, and adverse event reporting. Specific outcomes related to the rehabilitation triage clinic will be reported separately. Secondary outcomes are to examine the preliminary effectiveness of the neuro-oncology exercise program on patient-reported outcomes, functional fitness, and physical activity levels. We hypothesize that ACE-Neuro will be feasible, with ≥50% eligible patients referred to ACE-Neuro, ≥50% of those enrolled will complete the intervention, ≥60% of those who complete the intervention will complete pre- and post-intervention measures, ≥40% of those who complete the intervention will complete follow-up measures, and no major adverse events will occur. We also hypothesize that ACE-Neuro will be effective, as measured by improvements in patients’ physical and psychosocial well-being as well as physical activity levels (individual level outcomes), and a more integrated workflow in the clinical cancer care setting that includes exercise as part of standard clinical practice (systems level outcome).

## Methods

2

### Study design and procedure

2.1

This study was approved by the University of Calgary Health Research Ethics Board of Alberta (HREBA) – Cancer Committee (CC) - HREBA. CC-20-0322. Using the successful implementation model of the exercise oncology program developed in ACE, the proposed feasibility study includes a neuro-oncology cohort within a mixed methods study design.

### Participants

2.2

All neuro-oncology patients with a malignant or benign primary brain tumour that are pre, on, or completed treatment in Alberta, Canada, are >18 years, and able to consent in English are eligible to participate in the study. Recruitment began in April 2021 and is expected to close in Spring 2023, with follow-up assessments concluding a year later (Spring 2024). Because the main outcome of this study is feasibility, an *a priori* sample size has not been calculated. Based on current clinical numbers, and previous work done with neuro-oncology patients at CCI, we anticipate approximately 25–30 eligible patients per year, per site.

### Recruitment & referral

2.3

The study flow is depicted in Fig. 1. Our aim is to support referral of all eligible neuro-oncology patients to ACE-Neuro. Recruitment procedures are dependent on the site. Within Calgary (i.e., TBCC), the clinical team (consisting of oncologists and nurse practitioners) will send a referral to Rehabilitation Oncology via Cancer Care Alberta's *Putting Patients First Questionnaire* in the electronic oncology booking and medical information system. The clinical team, based on their judgment, may not refer patients they deem to be ineligible, for reasons such as disease status, not being interested, unable to participate in exercise, not able to consent in English, or other clinical reasons. In Edmonton (i.e., CCI), neuro-oncology patients will be introduced to ACE-Neuro during their usual triage assessment that is conducted by an occupational therapist. Patients will be provided with a study brochure and instructed to contact the study team.

**Fig. 1 fig1:**
[figure not shown]
Flow diagram for the multi-site single-arm ACE-Neuro study. Recruitment began in April 2021. Follow-up assessments are expected to conclude in Spring 2024. PROs = patient-reported outcomes.

Once referred to ACE-Neuro, the study coordinator at each site contacts potentially eligible patients and presents a full introduction to the study. Patients that agree to participate are sent the study consent form via REDCap, a secure web application (Research Electronic Data Capture; REDCap) [20]. After consenting to the study, all patients undergo a two-part screening procedure prior to beginning the exercise program. In Calgary, this procedure includes the following:(1)**CALGARY PART ONE SCREENING**: Patients will complete health and medical history screening, including a Health History Questionnaire, an Identifying Information Questionnaire (i.e., demographics), and the Physical Activity Readiness Questionnaire; PAR-Q+. In addition, patients complete baseline patient-reported outcomes (PROs), which are further outlined below. This screening and all questionnaires are completed via REDCap.(2)**CALGARY PART TWO SCREENING**: Cancer Physiatry (i.e., physical medicine and rehabilitation) is part of the Rehabilitation Oncology clinic team at the TBCC, thus patients will attend a Neuro Oncology Rehabilitation Triage Clinic, led by a Resident Physician ([name]) and the ACE-Neuro Study Coordinator ([name]), to assess the patients' readiness for participating in ACE-Neuro. During this 45-minute appointment, patient medical and functional history is reviewed, a full neurological examination is performed, and the Short Physical Performance Battery Protocol (SPPB) screening test is performed [21]. Based on test results, Karnofsky Performance Status (KPS) and Eastern Cooperative Oncology Group (ECOG) scores are determined and patients are subsequently triaged to ACE-Neuro, Rehabilitation Oncology (including physiatry, physiotherapy, and occupational therapy), or a combination of these services. If not initially triaged to ACE-Neuro, patients will be re-referred to the ACE-Neuro study team once deemed appropriate by their clinical team. During the COVID-19 pandemic, additional Alberta Health Services-regulated COVID-19 screening procedures will take place in advance of this in-person appointment.

In Edmonton, Cancer Physiatry is not internally offered as a Rehabilitation Oncology service within the cancer care system. Thus, as part of usual care, patients will be assessed by an occupational therapist, which includes completing the Short Physical Performance Battery screening test. Following self-referral to ACE-Neuro and participant consent to the study, the subsequent screening procedure includes:(1)**EDMONTON PART ONE SCREENING**: A Clinical Exercise Physiologist will complete health and medical screening for participants using the Health History Questionnaire, Identifying Information Questionnaire, and the Physical Activity Readiness Questionnaire; PAR-Q+.(2)**EDMONTON PART TWO SCREENING**: The Clinical Exercise Physiologist will obtain physician approval for participation in ACE-Neuro.

### The exercise intervention

2.4

#### Exercise sessions

2.4.1

Upon entering the study, participants will be provided with a welcome package including an overview of the 12-week program, the role of exercise for neuro-oncology, understanding the FITT (Frequency, Intensity, Time, and Type) principle, instructions for using the activity tracker, educational topics and their respective handouts, and additional resources, including a Cancer and Exercise Wellness Manual. The 12-week exercise intervention will be tailored to each participant, with programs designed by an exercise specialist (Fig. 2). Following published guidelines [1], and the established ACE [18], program protocol, the program will include twice-weekly supervised exercise sessions led by the study exercise specialist. Depending on COVID-19 restrictions and participant preferences, the intervention is delivered remotely (i.e., via Zoom), or in-person (i.e., at the University of Calgary or University of Alberta cancer and exercise-specific facilities). Session intensity will be based on participants' acute perceptions of energy and fatigue and monitored using Borg's Rating of Perceived Exertion (RPE; 1–10) scale [22]. Sessions will be 30–60 min, tailored to meet the unique needs of each individual and progressed over time, and overall may include the following: 5-10-min warm-up focusing on mobility and light aerobic movements (RPE ∼1–3); a 15-40-min aerobic, resistance, and balance training circuit (RPE ∼2–6); followed by a 10-15-min cool down, including flexibility training (RPE ∼1–2). All participants start in a one-on-one format, and after two weeks of individual sessions, participants are offered a once-weekly group in-person or virtual (depending on COVID-19 restrictions) session with other ACE-Neuro participants. If participating remotely, both one-on-one and group-based sessions will be delivered via Zoom. The group session will replace one of their weekly individual sessions, and is designed to foster social connections that are central to the ACE model [18]. Finally, the exercise program will follow an “*exercise and educate*” framework that is based on motivational interviewing, health coaching, and health behaviour change [23,24] that includes the education topics of (1) goal setting, (2) behaviour change, (3) stress management, (4) self-compassion, (5) sleep, and (6) social support. Education topics will be discussed every two weeks at the end of the exercise session, during cool-down. In addition, participants will have the option to attend a live webinar on each topic during their 12-week program.

**Fig. 2 fig2:**
[figure not shown]
Overview of exercise intervention components.

#### Health coaching

2.4.2

All participants will have the choice to participate in health coaching calls [23], provided by a health coach with exercise oncology specific training. Health coaching calls will take place weekly for 15–30 min following an individualized exercise training session, and will be delivered remotely (e.g., via end-to-end encrypted Zoom or phone call) at the participants’ preferred date and time. Health coaching calls will use a participant-centered approach, with consideration given to participant-determined discussion, self-discovery, and the coach-participant relationship [23]. Health coaching will be delivered one-on-one for the first month of the program (week 1–4), followed by group health coaching for the remainder of the 12 weeks (week 5–12), for the participants that attend the group-based classes.

To ensure consistency in both the health coaching and exercise program delivery across participants, and to ensure that the principles of health coaching are being followed during calls, fidelity checks will take place throughout the study. Ten percent of all calls and exercise sessions will be randomly selected for evaluation, and a standardized fidelity ‘checklist’ form will be completed by blind trained assessors (i.e., experts in the field; trained graduate students).

### Timeline of assessments

2.5

In addition to attending the triage clinic, consenting patients will complete assessments at five timepoints (1): baseline PROs and health screening, pre-triage clinic, (2) baseline functional fitness, post triage clinic, (3) post-program (twelve weeks), (5) six months, (6) twelve months (Fig. 1). The twelve week, six month, and twelve month timepoints will all include the completion of PROs via REDCap and the assessment of functional fitness (online via Zoom or in-person). Objective physical activity will only be collected during the intervention (baseline to twelve weeks). Participants recruited in Edmonton will complete assessments at four timepoints, as they do not attend the triage clinic (i.e., baseline PROs and functional fitness occur at the same time for participants in Edmonton; Fig. 1).

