##### Assessment of functional fitness

2.6.3.2

Assessments of functional fitness will follow the set protocols within the larger ACE study [18], and are designed to be able to be completed in-person or via remote delivery (online assessment). All fitness assessments will be completed by an exercise specialist and will include assessments of body composition, muscular strength, muscular endurance, balance, flexibility, and cardiorespiratory fitness. Given the online nature for the start of ACE-Neuro, only the online assessments are indicated here. See Supplementary File 1 for a table of the in-person assessments. For online assessments, resting heart rate will be measured by the study-provided activity tracker or via manual palpation. Resting blood pressure will be measured if the participant has an at-home blood pressure monitor. Participants’ height and weight measurements from the triage clinic (Calgary) or their most recent medical appointment (Edmonton) will be used. Muscular endurance will be measured by the 30 s sit-to-stand test [35,36]. Static balance will be measured by the single-leg-stance following the Canadian Society for Exercise Physiology (CSEP) protocol [37,38]. Flexibility will be measured using the sit and reach test [39,40] and the shoulder flexion test [41]. Cardiorespiratory fitness will be measured using the 2-Minute Step Test [42].

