#### Quantitative data

2.7.1

Descriptive characteristics of participants will be presented as mean ± standard deviation or percentages. Feasibility will be reported descriptively in relation to the pre-determined thresholds. We will investigate preliminary effectiveness of our secondary outcomes. Descriptive statistics will also be reported for feasibility numbers, PROs, functional fitness, and objective physical activity. Change scores will be calculated for PROs and functional fitness and to calculate power for a future fully-powered trial. Where available, the minimum clinically important difference (MCID) [52] will be reported as an indicator of clinical significance, which is appropriate for a pilot study.

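### Calgary's baseline PROs come before triage and are not repeated after delayed entry, so some PRO change scores include time outside the programme; a carried-forward online weight is a narrower, conditional problem

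*Protocol article*

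**What the plan says.** All references are to the protocol article.

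- **Calgary baseline, PROs.** Section 2.3 (the text after the Fig. 1 caption) places the PROs in part one screening, before the triage appointment: "In addition, patients complete baseline patient-reported outcomes (PROs), which are further outlined below". Section 2.5 confirms the order: "baseline PROs and health screening, pre-triage clinic, (2) baseline functional fitness, post triage clinic". The remaining timepoints are twelve weeks, six months and twelve months.
- **Triage outcome.** After the clinic, "patients are subsequently triaged to ACE-Neuro, Rehabilitation Oncology (including physiatry, physiotherapy, and occupational therapy), or a combination of these services". Then: "If not initially triaged to ACE-Neuro, patients will be re-referred to the ACE-Neuro study team once deemed appropriate by their clinical team".
- **Edmonton baseline.** Section 2.5: "baseline PROs and functional fitness occur at the same time for participants in Edmonton".
- **Body composition and weight.** Section 2.6.3.2 says the fitness assessments "will include assessments of body composition, muscular strength, muscular endurance, balance, flexibility, and cardiorespiratory fitness". For online assessments, "height and weight measurements from the triage clinic (Calgary) or their most recent medical appointment (Edmonton) will be used".
- **Use of the data.** Section 2.7.1: "Change scores will be calculated for PROs and functional fitness and to calculate power for a future fully-powered trial".

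**The concern.** The secondary pre-post changes are meant to describe what happens over a 12-week exercise programme. A Calgary patient sent first to physiatry, physiotherapy or occupational therapy has completed the PROs before that care begins. The later change score then combines the effect of that care, the passage of time with a brain tumour, and the programme itself. Section 2.2 admits patients before, during or after treatment, so a delay could also span a change of treatment phase.

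Two mismatches follow. Within a delayed Calgary patient, PRO change and fitness change start at different times. Between sites, the PRO baseline is defined differently. The study has a single arm, so no control group can separate these influences. Because the change scores are also tied to the power of a future trial, a distorted mean or SD would carry forward.

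The weight issue is separate. If one triage-clinic value serves both the baseline and the week-12 online assessment, the difference contains no information.

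**Working it through.** The article states no sample size, effect size or SD for these outcomes, so there is no figure of its own to reproduce. The check is one of measurement order, followed by illustrative arithmetic.

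**1. Order of events for a delayed Calgary patient (sections 2.3 and 2.5)**

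Consent → PROs (part one screening) → triage clinic → Rehabilitation Oncology → re-referral, with no stated time limit → programme → week-12 PROs and fitness. Baseline fitness falls somewhere after the triage clinic. The listed timepoints contain no PRO set between the clinic and week 12.

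**2. Share of the PRO interval outside the programme**

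Let g be the weeks from the baseline PROs to programme start (assumed; the article does not give it), with the 12-week PROs at the end of the programme.

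Interval = 12 + g; share outside the programme = g / (12 + g).

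| g (weeks, assumed) | Interval (weeks) | Share outside |
|---|---|---|
| 1 | 13 | 1/13 = 7.7% |
| 2 | 14 | 2/14 = 14.3% |
| 4 | 16 | 4/16 = 25% |
| 8 | 20 | 8/20 = 40% |
| 12 | 24 | 12/24 = 50% |

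These are per-patient shares of time, not estimates of bias in the study mean. The latter would also need the proportion of patients delayed and how PROs move during the delay; neither is given. With PROs taken at programme start, g = 0 and the share is 0%.

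**3. Weight, if the online rule also covers follow-up**

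For a Calgary participant assessed online at both visits: change = triage value − triage value = 0.

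To see the effect on a pooled summary, let a share f of participants have a carried-forward weight. In the others, assume a mean change δ = 1.0 and SD σ = 2.0 (illustrative values, not from the article).

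Mean = (1 − f)δ; SD = √[(1 − f)σ² + f(1 − f)δ²].

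| f (assumed) | Mean | SD | Mean/SD |
|---|---|---|---|
| 0 | 1.00 | 2.00 | 0.50 |
| 0.25 | 0.75 | 1.79 | 0.42 |
| 0.50 | 0.50 | 1.50 | 0.33 |
| 0.75 | 0.25 | 1.09 | 0.23 |
| 1 | 0 | 0 | undefined |

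Both the mean and the SD shrink, and so does the standardised change that a power calculation would use.

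**The case against.** The strongest reply is that this is a condensed article whose Fig. 1 is not shown, and that stale baselines and assessment windows are often handled in a full protocol or analysis plan. A re-referred patient returns to the study team, and the steps described after referral include the PROs, so a repeat may happen in practice. That is possible, but the article does not say so. It sets out the timepoints explicitly, with a single Calgary PRO baseline before triage. An analysis plan also cannot recover programme-entry PROs that were never collected.

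Other parts of the reply stand:

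- **Weight.** A reader might infer that every Calgary online change score, or at least every weight change, is zero by construction. The article does not support that. Sit-to-stand, single-leg stance, the flexibility tests and the step test are measured directly. The weight rule does not say the triage value is reused at follow-up, although it names no other online source for Calgary. In-person assessment is also available.
- **Edmonton.** It is tempting to treat Edmonton as already having a PRO baseline close to the first session. Section 2.5 says only that PROs and fitness coincide with each other; no interval to the first session is given at either site. No between-site comparison is described, so the difference matters mainly for pooling.
- **Direct entrants.** For patients triaged straight to ACE-Neuro the gap may be short.
- **Residual influences.** Rehabilitation may run alongside the programme, and cancer treatment may continue. A fresh baseline removes the pre-programme period but does not make a single-arm change causal.
- **Importance.** The secondary outcomes are descriptive and labelled preliminary, and section 3.1 concedes limited power.

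**Conclusion.** The concern holds for the Calgary PROs. As written, patients who enter after other rehabilitation have a PRO change that begins before that care, over an interval with no upper limit, and out of step with their own fitness change. With an assumed gap of 4 to 12 weeks, 25% to 50% of that interval lies outside the programme. This applies to the delayed subset only, whose size is unknown.

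The weight point is conditional. Weight change and any index derived from it are zero only for Calgary participants assessed online at both visits, and only if the section 2.6.3.2 rule covers follow-up. Edmonton's value can change between visits but is not tied to the assessment date.

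What is affected is the interpretation of preliminary effectiveness and the inputs to the future power calculation. Nothing here touches the primary feasibility outcome. The change is worth making because the loss cannot be repaired at analysis and prevention is cheap.

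**What to change.** 1. In Calgary, take the analysis-baseline PROs at the baseline fitness assessment. Alternatively, re-send the REDCap set there when the pre-triage set is older than a pre-set window, or when the patient was re-referred after other rehabilitation. Fourteen days is one example of a window; the choice is a judgement. Keep the pre-triage set for screening.
2. State how close the baseline fitness assessment is to the first exercise session at both sites, since step 1 relies on it.
3. For participants already enrolled, report the gap from baseline PROs to programme start and show PRO changes by gap.
4. Use a weight dated near each online assessment at both sites, or exclude online weight and its derived indices from the change scores.

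Cost: one repeat questionnaire set for a subset of Calgary participants, a dated weight field, and a short descriptive table. No extra visit is needed, because the baseline fitness assessment already exists.
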